### 9.2 Statistical and Analytical Plans

#### 9.2.1 General Considerations

Statistical analysis will be implemented using the IBM SPSS version 27.0. Before applying any statistical test, the data sets will be tested for a normal distribution with the Shapiro–Wilk test. If the data was found to be normally distributed, then one- way analysis of variance ANOVA and Student’s t-test will be used for the comparison between groups. Analysis of Covariance ANCOVA will be used to compare one or more means between groups

while controlling for the effects of one or more covariates (continuous variables that are related to the dependent variable). For comparison with the baseline value, paired t-test or one-way analysis of variance (ANOVA) will be used to compare the differences within the group before and after treatment. If the data was found to be not normally distributed then Kruskal-Wallis test or Mann-Whitney rank-sum test was used for the comparison. In order to correct for multiple comparisons, Bonferroni correction will be used to further validate the significance of each p-value. All statistical tests were conducted using a two-sided test. The  $\alpha$ -value was set to 0.05 for all the statistical tests and < 0.01 for Bonferroni correction. Chi-Squared test was used for categorical data, and Mann-Whitney rank sum test was used for ordinal data.

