### **2.2 Primary Objective and Outcome measures**

The primary objective is to evaluate the effectiveness of tPCS in addition to standard therapy in improving social functioning in children with ASD, aged 3 to 14 years old. The primary outcome measure will be the change in mean scores as measured by the Autism Treatment Evaluation Checklist (ATEC), for both ATEC total and subdomain scores, at post-treatment compared to baseline. The secondary outcome measure will be the change in mean scores as measured by the Autism Behaviour Checklist (ABC), for both ABC total and subdomain scores, at post-treatment compared to baseline.

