### Autism Treatment Evaluation Checklist (ATEC)

ATEC is developed by the Autism Research Institute and designed as a one-page checklist. Comprising 77 items, the ATEC has been utilized to assess the efficacy of interventions by measuring changes in response to various treatment modalities for children with ASD. The ATEC consists of four subscales totaling 77 items:

- Scale I: Speech, Language, and Communication (14 items, with scores ranging from 0 to 28)
- Scale II: Sociability (20 items, with scores ranging from 0 to 40)
- Scale III: Sensory and Cognitive Awareness (18 items, with scores ranging from 0 to 36)
- Scale IV: Health, Physical Condition, and Behavior (25 items, with scores ranging from 0 to 75)

Each category within the ATEC utilizes a four-point rating scale to gauge the severity of issues, ranging from 0 (indicating no problem) to 3 (indicating a serious problem). The ATEC generates a total score ranging from 0 to 179, with higher scores indicating a greater degree of reported activity limitations. This comprehensive assessment tool enables researchers and clinicians to gain insight into the challenges faced by individuals with ASD and to monitor changes in symptoms and functioning over time. For this study, the ATEC will be administered twice (pre- and post-tPCS) and carried out by an experienced therapist or doctor who is blinded regarding the subject allocation.

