## **A5.3 Statistical interim analyses:**

Primary outcome measure: Autism Treatment Evaluation Checklist (ATEC) total and subdomain scores will be used for analysis of change in social functioning. T-tests, ANOVA and ANCOVA will be used to examine the rate of improvement for these scores. Scores will be compared with baseline. Estimates of the difference in the average rate of improvement in the scores will be obtained. These estimates will then be tested against the null value of no difference between both groups.

Secondary Outcome measures: Autism Behaviour Checklist (ABC) total and subdomain scores will be used for analysis of change in social functioning. The Childhood Sleep Habits Questionnaire (CSHQ) will be used for analysis of change in sleep functions. Scores will be compared with baseline. Estimates of the difference in the average rate of improvement in the scores will be obtained. These estimates will then be tested against the null value of no difference between both groups.

Participant characteristics at baseline (including demographic and clinical) will be compared within each group using independent sample t-tests or chi-square test as appropriate for the variable.

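### A normality pre-test on unspecified data chooses the between-arm test, and no baseline-adjusted analysis is fixed as primary

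*Combined protocol and SAP*

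**What the plan says.** Section 9.2.1 of the combined protocol and SAP opens with the rule "Before applying any statistical test, the data sets will be tested for a normal distribution with the" Shapiro–Wilk test. Two routes follow.

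- **Pass:** "If the data was found to be normally distributed, then one- way analysis of variance ANOVA and" Student's t-test are used between groups.
- **Fail:** "If the data was found to be not normally distributed then Kruskal-Wallis test or Mann-Whitney rank-sum test was used for the comparison".

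Between the two stands a separate sentence: "Analysis of Covariance ANCOVA will be used to compare one or more means between groups", controlling for covariates. It lists no covariate, carries no normality condition, and does not make ANCOVA the primary analysis.

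The section leaves open whether the pre-test is applied to baseline, post-treatment or change scores or to residuals, whether arms are pooled, and at what level the pre-test is judged.

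Section 2.2 defines the primary outcome as the change in mean ATEC score, "for both ATEC total and subdomain scores, at post-treatment compared to baseline". That makes five scores, one total and four subdomains. Appendix 5, section A5.3, gives the interim method for ATEC without any pre-test or rank route: "T-tests, ANOVA and ANCOVA will be used to examine the rate of improvement for these scores".

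**The concern.** A confirmatory analysis should be identifiable before the data are seen. Here the between-arm test, and with it the quantity being compared, depends on the p-value of a preliminary test whose input is undefined. Three things are at stake.

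- **What is estimated.** A t-test or ANCOVA compares means, which matches section 2.2. Mann–Whitney compares distributions by rank and yields no mean difference. If some ATEC scores pass and others fail, scores listed together as primary are judged by different hypotheses.
- **What triggers the switch.** Shapiro–Wilk becomes more sensitive as the sample grows, while the mean-based tests become less dependent on normality. At this trial's size the pre-test can divert the analysis over departures that do no harm.
- **Efficiency.** A baseline value exists for every score, but no route commits the trial to adjusting for it.

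**Working it through.** **Inputs from the documents.** Effect size 0.36, 80% power, 120 per group, 40% dropout (section 9.1); 170 per group randomised (section 4.2); two-sided tests at 0.05 (section 9.2.1); ATEC total 0–179, narrowest subscale 0–28 (section 4.3, ATEC note). With 40% dropout, 170 × 0.6 = 102 per arm remain, so the range of interest is 102 to 170 per arm.

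**Assumptions, because the documents give no figure.** SD of the score tested: 2 to 20 points. Skewness: 0.5 as a mild case. Baseline–post correlation ρ: 0.5 to 0.9. Pre-test level: 0.05.

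**1. The plan's own figure.** For a two-sided comparison of two independent groups, n = 2(1.96 + 0.8416)² / 0.36² = 121.1, or 122 per group. This is close to the stated 120, so 0.36 is used below as a two-group effect size.

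**2. How often does rounding alone fail the pre-test?** Normal data rounded to whole points, simulated share failing Shapiro–Wilk:

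| SD (points) | n = 120 | n = 170 |
|---|---|---|
| 2 | 98% | 100% |
| 2.5 | 65% | 94% |
| 3 | 34% | 61% |
| 4 | 16% | 24% |
| 5 | 11% | 12% |
| 10 | 6% | 7% |
| 20 | 5% | 6% |

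At n = 102, SD 3 gives about 27–30%. Rounding therefore matters at an SD of about 3 or less and is close to the nominal 5% at SD 10 or more.

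**3. How often does mild skewness fail it?** With skewness 0.5, about 43% of arms fail at n = 102 and 64% at n = 170. If either arm failing sends the score to ranks, the chance is 1 − (1 − 0.43)² = 67% to 1 − (1 − 0.64)² = 87%. Repeat runs on scores rounded at SD 10 gave 71–90%. This does not need a narrow scale: at SD 20 and 120 per arm the figure was 74–76%.

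**4. Does the mean-based test need protecting?** With skewness 0.5 and 120 per arm, the t-test's simulated type I error was 4.5–5.6%. For ANCOVA it stayed at about 5–6% up to skewness 1.5. The pre-test-then-choose procedure itself had type I error of 4.4–5.6%, with power within about 2 points of the t-test. The t-test and Mann–Whitney reached different verdicts in about 2% of null trials and 3–6% at an effect of 0.36.

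**5. Power at 102 per arm, effect 0.36 SD of change.** Power ≈ Φ(δ√(n/2) − 1.96).

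- t-test on change: 0.36 × √51 = 2.571, giving Φ(0.611) = 73%.
- Mann–Whitney on change, normal data: n is multiplied by 3/π = 0.955, giving 97.4. Then 0.36 × √48.7 = 2.512, giving Φ(0.552) = 71%.
- ANCOVA: the variance falls by the factor (1 + ρ)/2 relative to the change score, so δ is multiplied by √(2/(1 + ρ)).

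| ρ | δ√(n/2) | ANCOVA power | Gain over Mann–Whitney |
|---|---|---|---|
| 0.5 | 2.571 × 1.155 = 2.969 | 84% | 13 points |
| 0.7 | 2.571 × 1.085 = 2.789 | 80% | 9 points |
| 0.8 | 2.571 × 1.054 = 2.710 | 77% | 6 points |
| 0.9 | 2.571 × 1.026 = 2.638 | 75% | 4 points |

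Simulation gives much the same: 74–83% for ANCOVA, 72–73% for the t-test and 69–72% for Mann–Whitney, a gain of about 4–12 points over Mann–Whitney. Against the t-test on change the ANCOVA gain is about 2 to 11 points by the formula (75 − 73 to 84 − 73).

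**The case against.** The strongest reply is that the pre-test does little measurable harm: type I error is held, and the t-versus-rank choice costs about 1–3 points of power. That stands. Most of the power gap arises because ANCOVA is not fixed as primary on either route, not because of the Shapiro–Wilk step. For a strongly skewed score (skewness about 1.5) a rank test would do better, with simulated power of 87–99% against 84–95%.

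Four stronger readings are tempting, and the documents do not support them.

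- *Rounding of whole-number scores decides the primary test.* This needs an SD of about 3 points or less. No SD is given, and on a 0–179 total with an SD of 10 or more the effect is negligible.
- *Baseline adjustment is lost on the rank route.* Mann–Whitney applied to change scores still subtracts baseline, and the ANCOVA sentence in section 9.2.1 is not conditional on normality. The adjustment is unspecified, not excluded.
- *The pre-test is run on raw scores, score by score.* The text refers only to data sets, so both details are inferences. So is the rule in step 3 that one failing arm is enough.
- *The sentence "Mann-Whitney rank sum test was used for ordinal data" contradicts the t-test route for ATEC.* The plan nowhere classes the summed scores as ordinal, and sections 2.2 and A5.3 treat ATEC as a score compared by means.

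None of this answers the central point: nothing in the plan names the test that will be the primary one.

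**Conclusion.** The point holds as a matter of pre-specification and efficiency. It is not a threat to type I error. The between-arm test for ATEC depends on a pre-test of undefined data. Under assumed skewness of 0.5 that pre-test would fail in at least one arm in roughly two thirds to nearly nine tenths of trials, at sample sizes where normality is not needed. The cost is an effect measure that may not match section 2.2 and may differ among the five ATEC scores. It also forgoes about 4–12 points of power if Mann–Whitney on change is used where ANCOVA could have been fixed. The power figures rest on 102 per arm, an effect of 0.36 SD of change and correlation 0.9 to 0.5. The correlation and the skewness are assumptions, not figures from the documents.

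**What to change.** In section 9.2.1, delete the Shapiro–Wilk step as the selector of the between-arm test for ATEC, ABC and CSHQ. State one primary analysis for every score: a linear model of the post-treatment score on arm and the baseline value of the same score, reporting the adjusted mean difference with a 95% confidence interval. A robust or bootstrap interval is optional. With baseline in the model, the arm estimate is the same whether the post-treatment or the change score is the response, so this stays in line with section 2.2. Check residual plots. Keep a rank-based analysis only as a sensitivity analysis that cannot replace the primary one.

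The cost is wording: no new data and no change in sample size. The downside is some loss of power for a strongly skewed score (skewness about 1.5), which the sensitivity analysis would show.

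### No single primary between-arm test of ATEC is named, and the plan never commits to adjusting for the baseline ATEC that it collects in every child

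*Combined protocol and SAP*

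**What the plan says.** Section 2.2 sets the endpoint: "The primary outcome measure will be the change in mean scores as measured by the Autism Treatment Evaluation Checklist (ATEC"), for total and subdomain scores, post-treatment against baseline.

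Section 9.2.1 gives one generic list of methods for all endpoints:

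- If the data pass a Shapiro–Wilk test, one-way ANOVA and the t-test apply, and ANCOVA follows in the next sentence. In the section's words, the first two "will be used for the comparison between groups. Analysis of Covariance ANCOVA will be used to compare one or more means between groups".
- The ANCOVA adjustment is described only in general terms: "while controlling for the effects of one or more covariates (continuous variables that are related to the dependent variable"). No covariate is named.
- "If the data was found to be not normally distributed then Kruskal-Wallis test or Mann-Whitney rank-sum test was used for the comparison".

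Section A5.3, on the interim analysis, says of the ATEC scores that "T-tests, ANOVA and ANCOVA will be used to examine the rate of improvement for these scores". It adds that scores are compared with baseline and that the difference between groups is tested against zero.

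Baseline data will exist. Section 4.3 schedules ATEC, ABC and CSHQ at Visit 1 and Visit 22, and its ATEC note confirms that "the ATEC will be administered twice (pre- and post-tPCS").

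**The concern.** A confirmatory trial needs one analysis, fixed in advance, that decides the primary question. Here an unadjusted test, a covariate-adjusted test with an open covariate list and a rank test all qualify, and no text ranks them. Two things are at stake.

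- **Precision.** Baseline enters the endpoint by subtraction. That is not the same as adjusting for it, and under randomization it is less efficient unless the baseline-to-post correlation is close to 1. The plan allows for 40% dropout, so the gain is worth securing.
- **Flexibility.** The permitted tests can fall on different sides of 0.05. If the choice is made after the data are seen, the nominal 5% no longer describes the procedure. The interim look at 170 children uses the same open list, so the choice could still be open after between-arm results have been presented.

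**Working it through.** **Inputs from the documents.** Effect size 0.36, 80% power, 120 per group, 40% dropout and 340 recruited (section 9.1); two-sided 0.05 (section 9.2.1); 1:1 allocation (section 4). Completers per arm if 40% drop out: 340 × 0.6 / 2 = 102.

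**Assumed.** The correlation r between baseline and Visit 22 ATEC is not given. I use 0.5 to 0.9, equal variances at the two visits, and 0.36 in SD units of the change score.

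**The plan's own figure.** An unadjusted two-sample, two-sided comparison needs n = 2(1.96 + 0.8416)² / 0.36² = 121.1, so 122 per arm. This is close to the stated 120, so the planned size takes no credit for baseline adjustment. (The paired and one-sided wording in section 9.1 does not give 120: one-sided two-sample gives 96 per arm, and paired two-sided gives 63. That is a separate matter.)

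**How many different tests there are.** With two arms, one-way ANOVA and the equal-variance t-test are the same test (F = t²); a numerical check gave the same p-value, 0.0258. The real choice is unadjusted, ANCOVA or rank test.

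**Precision.** In units of the single-visit variance, the change score has variance 2(1 − r) and ANCOVA on baseline has 1 − r². The ratio is 2(1 − r)/(1 − r²) = 2/(1 + r). ANCOVA power by the normal approximation is Φ(0.36 × √(2/(1 + r)) × √(n/2) − 1.96). For the unadjusted test at n = 102: 0.36 × √51 = 2.571, and Φ(0.611) = 0.729. For ANCOVA at r = 0.5: 2.571 × √1.333 = 2.969, and Φ(1.009) = 0.843.

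| Analysis | Variance of change-score test ÷ ANCOVA | n per arm for 80% power | Power at 120 per arm | Power at 102 per arm |
|---|---|---|---|---|
| Unadjusted change score | – | 122 | 80% | 73% |
| ANCOVA, r = 0.5 | 1.33 | 91 | 90% | 84% |
| ANCOVA, r = 0.7 | 1.18 | 103 | 86% | 80% |
| ANCOVA, r = 0.8 | 1.11 | 110 | 84% | 77% |
| ANCOVA, r = 0.9 | 1.05 | 116 | 82% | 75% |

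**False positives when the better result is quoted.** I simulated trials with no true effect, two-sided 0.05, 120 per arm and 20,000 trials for each r. Every single test held about 5%. The last column adds a true effect of 0.36 (5,000 trials for each r).

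| r | Change-score t-test or ANCOVA significant | Rank test on change added | t-test and ANCOVA disagree on significance, true effect 0.36 |
|---|---|---|---|
| 0.5 | 7.4% | 8.1% | 12% |
| 0.7 | 7.0% | 7.8% | 10% |
| 0.9 | 6.0% | 6.8% | 5% |

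Theory agrees. Under the null the two statistics have correlation √((1 + r)/2), that is 0.866, 0.922 and 0.975. The bivariate normal probability that at least one exceeds 1.96 in size is then 7.3%, 6.8% and 6.0%. Rounded outward, the range is about 5.5% to 7.5%. At r = 0.3 the simulated rate with the rank test is 8.5%.

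**The case against.** The strongest reply is that ANCOVA is already in the plan, every listed test is valid under randomization, and the loss is conditional. That is right as far as it goes. Precision is lost only if the unadjusted result is the one quoted, and at r = 0.9 the loss is about 5% of variance and two points of power. For a checklist repeated after four weeks, a high r cannot be excluded. What stands is that nothing in the text settles which result will be quoted.

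Section 9.2.1 also mentions a Bonferroni threshold of 0.01. That rule concerns multiple comparisons; it does not choose between tests of one comparison.

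A reader might infer four stronger points that the documents do not support:

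- **The false-positive rate doubles.** Adding a t-test on the post-treatment score alone does bring the simulated rate to about 10% to 11%. But section 2.2 defines the endpoint as change and section A5.3 compares scores with baseline. No text proposes a post-score-only test.
- **There are three competing parametric tests.** The t-test and one-way ANOVA coincide with two arms.
- **Covariates will be picked from the data.** The parenthesis in section 9.2.1 can be read as a general definition of a covariate, and no selection step is described. The supportable point is that none is named.
- **The primary endpoint is an unadjusted change.** Section 2.2 is silent on adjustment.

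**Conclusion.** The concern holds in a measured form. The between-arm ATEC comparison has no designated primary test and no named covariate, and the plan does not commit to baseline adjustment. For r between 0.5 and 0.9, an unadjusted change-score test carries 5% to 33% more variance than baseline ANCOVA. At 102 completers per arm, this is 73% power against 75% to 84%. Leaving the choice open puts the false-positive rate at roughly 5.5% to 7.5%, or about 7% to 8.5% with the rank test.

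These sizes rest on an assumed r, on 0.36 being in change-score SD units, and on the worst case in which the most favourable result is quoted. They leave out any free choice of ANCOVA covariates, which the documents give no means to quantify. No single listed test is biased; the defects are lost efficiency and an open choice.

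**What to change.** In sections 9.2.1 and A5.3:

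1. Name one primary between-arm analysis: ANCOVA of the Visit 22 ATEC total on arm and that child's baseline ATEC total, reported as the adjusted mean difference in ATEC points with a 95% CI. Modelling the change with the same baseline covariate gives the same treatment estimate, so this stays consistent with the change endpoint in section 2.2.
2. Use the same model for ABC and CSHQ, each with its own baseline.
3. List any further covariate in advance. Age is an option, not a requirement. Delete the wording that describes covariates only by their relation to the outcome.
4. Label the unadjusted t-test/ANOVA and the rank tests as sensitivity analyses, so that the Shapiro–Wilk result no longer selects the primary test.

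The cost is wording only. The baseline scores are already collected at Visit 1, and the planned software fits the model. The change should be made before any between-arm result is seen.

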### **9.2.2 Analysis of dropout cases**

The overall dropout rate was compared to the dropout rate due to adverse events using the Chi-Squared test; Cases lost to follow-up and patients who stopped the trial voluntarily should be included in the analysis of dropout cases.

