### 3.7 Drop-out Criteria

- A. Subjects that withdrew midway due to adverse events
- B. Subjects where treatment was interrupted for more than 7 days during the study, due to sickness such as acute respiratory tract infection.
- C. Subjects who failed to complete the course of treatment due to poor compliance or unexpected changes in parents' demands.
- D. Subjects whose circumstances no longer adhere to the inclusion and exclusion criteria midway through the trial, Eg. non-compliance of treatment protocol, subjects who begin a drug or treatment course in the exclusion criteria, without informing the study team.
- E. Cases where significant human errors were involved including administration of incorrect treatment dose and not being assessed according to the evaluation standards set in this trial during the pre- and post-treatment assessments.
- F. Subjects with significant missing items in the pre- and post-evaluations resulting in incomplete data.

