## 4.2 Randomization - Allocation Implementation

Subjects who meet the inclusion criteria and have signed consent form will be numbered according to their sequence of the time of visit (from 1 to 340). The administrator will send out the envelope with number corresponding to the number of the subject to the respective hospital of the subject. Upon opening of the envelope, the group allocation is revealed, and the subject is randomized to either the Control (Sham-tPCS) Group or the Intervention (active-tPCS) Group, with 170 subjects in each group.

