## 9 Sample Size and Statistical Methods

### 9.1 Determination of Sample Size

Based on a two-sided paired t-test at 80% power, 5% one-sided alpha and an expected effect size of small (0.20) when using bilateral frontal montage and medium (0.52) when using prefrontal-cerebellar montage, we will use an average of 0.36 effect size to compute the sample size, which leads to 120 per group. Based on an estimated 40% drop-out rate due to potential implications from post- COVID heightened travelling restrictions in Guangdong province, a sample size of 339 is required. We will use 340 as the sample size for recruitment in this study.

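### The dropout test in section 9.2.2 sets overall dropout against its own adverse-event subset and ignores treatment arm, so it cannot show differential attrition

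*Combined protocol and SAP*

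**What the plan says.** Section 9.2.2 is the only place that plans an analysis of dropout. It reads: "The overall dropout rate was compared to the dropout rate due to adverse events using the Chi-Squared test", and adds: "Cases lost to follow-up and patients who stopped the trial voluntarily should be included in the analysis of dropout cases". Neither statement mentions treatment arm.

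Section 3.7 lists six drop-out criteria, A to F. Criterion A is "Subjects that withdrew midway due to adverse events". The others cover interruption by illness, failure to complete treatment, loss of eligibility, serious error in treatment or assessment, and incomplete evaluations. (Section 3.8 refers the definition of dropout to clause 3.6, which holds the exclusion criteria. I take 3.7 to be meant.)

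Section 9.1 sets the planned attrition: "Based on an estimated 40% drop-out rate due to potential implications from post- COVID heightened travelling restrictions in Guangdong province". It concludes: "We will use 340 as the sample size for recruitment in this study". Section 4.2 allocates these children "with 170 subjects in each group". The Protocol Deviations note gives a range of 30% to 40%. No expected split of dropout by arm or by cause is given.

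Nearby text does not fill the gap. Section 9.2.3 compares adverse-event incidence between the two groups, but not dropout. Section 9.2.1 assigns chi-squared to categorical data in general. Sections 3.8 and 4.4 have reasons for leaving recorded, without an analysis by arm. Appendix 5, A5.3, covers outcome scores and baseline characteristics.

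**The concern.** A chi-squared test of two proportions compares two separate groups. Here both rates are taken over the same children, and every adverse-event dropout is counted in both numerators. The only thing that can separate the two rates is the number of children who left for some other reason, and the plan already expects such children, since it names loss to follow-up and voluntary withdrawal.

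The useful question is whether active and sham lose different numbers of children, or lose them for different reasons. Section 3.8 leaves the imputation for the intention-to-treat analysis unspecified, so attrition by arm and by reason is part of what a reader needs to judge that imputation. Several criteria in 3.7 also call for judgement at the site, where the envelope is opened (section 4.2). Section 6.4 lists participants, families and assessors as blinded, but not the staff who deliver stimulation. Dropout for adverse events is also a tolerability signal in its own right. As written, the analysis would report none of this by arm.

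**Working it through.** The plan attaches no figure to this test, so there is none to reproduce.

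**Inputs from the documents.** Total 340 (9.1); 170 per arm (4.2); dropout 40% (9.1), so 0.40 × 340 = 136; lower end 30% (Protocol Deviations), so 0.30 × 340 = 102; two-sided alpha 0.05 (9.2.1).

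**Assumptions.** The number of adverse-event dropouts and the split by arm are mine, and are varied below.

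**Formula.** For two proportions x/n and y/n, Pearson chi-squared without continuity correction is (x/n − y/n)² / [p(1 − p) × 2/n], with p = (x + y)/(2n).

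**1. What the stated test measures.** Let T be all dropouts and E those due to adverse events. Since E is contained in T, the difference in rates is (T − E)/340, the proportion leaving for other reasons. The null of equal rates holds only if T − E = 0. Arm appears nowhere in the expression.

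**2. The stated test at T = 136, E = 14.** p = 150/680 = 0.2206; difference = 122/340 = 0.3588; variance = 0.2206 × 0.7794 × 2/340 = 0.001011; chi-squared = 0.1288/0.001011 = 127.3 (p about 1.6 × 10⁻²⁹). The standard error used is √0.001011 = 0.0318. The difference is really a single proportion with standard error √(0.3588 × 0.6412/340) = 0.0260, so the overlap makes the variance wrong as well.

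**3. The same 136 dropouts, split by arm (170 per arm).** For 85 against 51: p = 0.40; difference = 0.20; variance = 0.24 × 2/170 = 0.002824; chi-squared = 0.04/0.002824 = 14.17.

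| Active / sham dropouts | Rates | Stated test (E = 14) | Active vs sham |
|---|---|---|---|
| 68 / 68 | 40% / 40% | 127.3 | 0.0, p = 1.00 |
| 80 / 56 | 47% / 33% | 127.3 | 7.06, p = 0.008 |
| 85 / 51 | 50% / 30% | 127.3 | 14.17, p = 0.0002 |
| 102 / 34 | 60% / 20% | 127.3 | 56.7, p = 5 × 10⁻¹⁴ |

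The same holds for adverse-event dropout. Splitting the 14 as 12 against 2 gives an arm comparison of chi-squared 7.45, p = 0.006 (Fisher's exact p = 0.011); the stated test stays at 127.3.

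**4. Varying the adverse-event count in the stated test.**

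| T | E | Chi-squared | p |
|---|---|---|---|
| 136 | 6 | 150.4 | 1 × 10⁻³⁴ |
| 136 | 34 | 81.6 | 2 × 10⁻¹⁹ |
| 136 | 68 | 32.4 | 1 × 10⁻⁸ |
| 136 | 102 | 7.5 | 0.006 |
| 102 | 10 | 90.5 | 2 × 10⁻²¹ |

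**5. Simulation, 20,000 runs.** The table gives the share of runs that reject at 0.05.

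| Dropout, active / sham | Adverse-event share of dropouts | Stated test | Active vs sham |
|---|---|---|---|
| 40% / 40% | 10%, 50%, 90% | 100%, 100%, 0.2% | about 5% in each |
| 50% / 30% | 10%, 50%, 90% | 100%, 100%, 0.3% | about 97% in each |

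The stated test follows the adverse-event share and is indifferent to arm.

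**6. What an arm comparison can and cannot show.** With 170 per arm, power is 47% for 45% against 35%, 81% for 47.5% against 32.5%, and 97% for 50% against 30%. A non-significant result is therefore weak reassurance, which is why the interval and the table of reasons matter more than the p-value.

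**The case against.** The strongest defence is that the sentence is loosely worded and was meant to say that overall dropout and adverse-event dropout would each be compared between groups. The neighbouring sections support this: 9.2.1 speaks of comparisons between groups and assigns chi-squared to categorical data, and 9.2.3 compares adverse-event incidence between the two groups. This may well be the intention. But 9.2.2 names two rates and no arms, and an analyst who follows it would run the wrong test. The defence is a reason to correct the sentence, and the general rule in 9.2.1 permits an arm comparison without committing to one.

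Tolerability is also partly covered, through the between-group test of adverse-event incidence, and the recorded reasons mean that a table by arm could be made in any case. Both are true, but neither is a planned comparison of dropout.

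Four stronger readings are tempting, and the documents do not support them.

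- A reader might call the null meaningless. It has a meaning, namely that no child leaves for any reason other than an adverse event. It is trivially false and uninformative.
- A reader might say that the stated test is always significant. At a 90% adverse-event share it rejects only about 0.2% of the time, even though its null is false.
- A reader might treat this as the main check on the validity of the primary result. Equal rates do not show that missingness is ignorable, and unequal rates do not by themselves show bias. The unspecified imputation in 3.8 weighs more.
- A reader might infer that attrition will differ by arm. The plan attributes its 40% to travel restrictions, which gives no particular reason to expect an imbalance, though it does not exclude one.

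**Conclusion.** The point holds for the text as written. The subset relation and the absence of arm follow from 9.2.2 and 3.7 alone and depend on no assumed number. The failure of independence and the trivially false null follow from the subset relation; the inability to show differential attrition follows from the absence of arm.

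The size is illustrative, because the documents give no split by cause or arm. At the planned 40% dropout with 14 adverse-event dropouts assumed, the stated test returns 127.3 for arm differences anywhere from 0 to 40 percentage points.

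The consequence is moderate. This is an ancillary analysis; correcting it alters neither the primary estimate nor its p-value. It should still be corrected, because dropout of 30% to 40% is expected and the reader will need attrition by arm and reason to interpret the primary result and whatever imputation is used.

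**What to change.** Replace the first statement of section 9.2.2 with:

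> Overall dropout and dropout due to adverse events will each be compared between active and sham as a risk difference with 95% CI and a chi-squared test (Fisher's exact test if expected counts are small), with reasons for dropout tabulated by arm.

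Keep the existing instruction to count losses to follow-up and voluntary withdrawals. Chi-squared is already the plan's method for categorical data and is adequate for overall dropout at 170 per arm; the exact test is needed only for sparse reasons. A table of baseline characteristics of drop-outs and completers by arm would be a useful optional addition.

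The cost is one sentence. Reasons for dropout are already collected under sections 3.8 and 4.4, so no new data are needed. If follow-up is complete, the same table can be produced at reporting, with the date of the change stated.
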